## Abstract

**Background:**

Intimate partner violence (IPV) against women in the United States (US) remains a complex public health crisis. Women who experience IPV are among the most vulnerable patients seen in primary care. Screening increases the detection of IPV and, when paired with appropriate response interventions, can mitigate the health effects of IPV. The Department of Veterans Affairs (VA) has encouraged evidence-based IPV screening programs since 2014, yet adoption is modest and questions remain regarding the optimal ways to implement these practices, which are not yet available within the majority of VA primary care clinics.

**Methods/design:**

This paper describes the planned evaluation of VA’s nationwide implementation of IPV screening programs in primary care clinics through a randomized implementation-effectiveness hybrid type 2 trial. With the support of our VA operational partners, we propose a stepped wedge design to compare the impact of two implementation strategies of differing intensities (toolkit + implementation as usual vs. toolkit + implementation facilitation) and investigate the clinical effectiveness of IPV screening programs. Using balanced randomization, 16–20 VA Medical Centers will be assigned to receive implementation facilitation in one of three waves, with implementation support lasting 6 months. Implementation facilitation in this effort consists of the coordinated efforts of the two types of facilitators, external and internal. Implementation facilitation is compared to dissemination of a toolkit plus implementation as usual. We propose a mixed methods approach to collect quantitative (clinical records data) and qualitative (key informant interviews) implementation outcomes, as well as quantitative (clinical records data) clinical effectiveness outcomes. We will supplement these data collection methods with provider surveys to assess discrete implementation strategies used before, during, and following implementation facilitation. The integrated-Promoting Action on Research Implementation in Health Services (i-PARIHS) framework will guide the qualitative data collection and analysis. Summative data will be analyzed using the Reach Effectiveness Adoption Implementation Maintenance (RE-AIM) framework.

**Discussion:**

This research will advance national VHA efforts by identifying the practices and strategies useful for enhancing the implementation of IPV screening programs, thereby ultimately improving services for and health of women seen in primary care.

**Trial registration:**

NCT04106193. Registered on 23 September 2019.

Contributions to the literature
Women who experience intimate partner violence (IPV) are among the most vulnerable patients seen in primary care. IPV screening programs are effective in detecting IPV and connecting women to care, but we need to understand how to systematically and effectively implement IPV screening programs in busy primary care settings.A cluster randomized, stepped wedge, hybrid type 2 implementation-effectiveness design will evaluate implementation and clinical effectiveness outcomes.A mixed method examination of implementation strategies associated with implementation facilitation and mapping them to the Expert Recommendations for Implementing Change compilation will advance implementation science.

## Background

Intimate partner violence (IPV) against women, defined as psychological, physical, and sexual aggression from a past or current intimate partner, is a complex public health problem. Although men also experience IPV, women are more likely to experience severe violence and to face more physical and mental health-related impacts [1, 2]. Nearly 7 million women are physically assaulted, raped, or stalked by an intimate partner in the USA annually [1], and IPV is strongly associated with poorer physical, psychological, and social health [3, 4]. Physical health problems range from injuries directly caused by physical and sexual assaults, to other chronic nervous system, cardiovascular, and reproductive conditions [5, 6]. Psychological problems include posttraumatic stress disorder, depression, anxiety, substance abuse, and suicidality [5–7]. Women who experience IPV are 2.4 times more likely to attempt suicide than those who do not experience IPV [8]. Social consequences include homelessness, financial insecurity, and unemployment [9–12]. The burden of IPV on women and society underscores the need for a feasible and effective health care response [13, 14].

Women who experience IPV present frequently to primary care [15–17], which is recognized as an ideal setting for safely identifying women who experience IPV and offering them resources and referrals to health and social services [18]. The United States Preventive Services Task Force [18] and recent research have found evidence that routine screening—paired with an appropriate response to disclosure—can reduce IPV and physical and mental health harms in women of childbearing age [19, 20]. One study found that women who talked to a provider about IPV were four times more likely to use an intervention and 2.6 times more likely to exit the relationship [21].

Routine screening for IPV in primary care is important for the US Department of Veterans Affairs (VA) medical centers, as nearly one in five (19%) Women Veterans (WVs) seen in primary care have experienced IPV in the past year [17] and IPV is more prevalent among WVs compared to women who have not served in the military [22]. Screening WVs for IPV is vital because formative research demonstrates that WVs want to be asked and are more likely to disclose when asked directly [23, 24]. Thus, VA recommends an evidence-based, trauma-informed, and patient-centered approach to IPV screening programs, including respect for patient privacy and autonomy, with an emphasis on three components: IPV screening on an annual basis, brief risk assessment and provision of resources for WVs who report experiencing IPV, and psychosocial service referrals (when desired by patients) [25].

A growing number of VA-based women’s specific primary care clinics have established IPV screening practices consistent with these recommendations [26, 27]. Yet, about two thirds of WVs accessing primary care services in VA do so in mixed-gender clinics or those that share space with clinics that predominantly treat men, such clinics have been slower to adopt evidence-based IPV screening practices. As such, there is a current disparity in the access to IPV screening programs for women seen in mixed-gender settings. To meet this need, in 2018, the study investigators launched a partnership with VA’s Office of Women’s Health Services and the IPV Assistance Program of Care Mangement and Social Work Services to evaluate the implementation of IPV screening practices for WVs in mixed-gender (model 1) and shared space (model 2) primary care clinics. In this manuscript, we describe the recently funded randomized program evaluation trial stemming from these efforts.

## Methods

### Overview

We have designed a stepped wedge hybrid type 2 implementation-effectiveness cluster randomized trial [28] to investigate both implementation and clinical effectiveness outcomes associated with the rollout of evidence-based IPV screening programs for WVs in VA-based mixed-gender and shared-space primary care clinics. We have received approval from the VA Boston Healthcare System’s Institutional Review Board (IRB) for all study procedures to evaluate this operations-led effort. The integrated-Promoting Action on Research Implementation in Health Services (i-PARIHS) framework [29] will guide the qualitative data collection and analysis. Summative data will be analyzed using the Reach Effectiveness Adoption Implementation Maintenance (RE-AIM) framework [30].

### Aims

For this study, we will be comparing two distinct implementation strategies to support the uptake of IPV screening programs. First, all sites will receive a toolkit designed by the IPV Assistance Program, to be distributed to local staff responsible for encouraging IPV screening in primary care (toolkit plus implementation as usual [IAU]). Second, consistent with our stepped wedge design, during the study, each site will be assigned (in a staggered fashion) to cross over to more intensive implementation support in the form of implementation facilitation [31]. Implementation facilitation will entail external Office of Women’s Health Services experts working directly with the local primary care staff at participating sites to encourage IPV screening uptake and will also involve toolkit dissemination (toolkit plus implementation facilitation).

An additional aim of the study will be to compare two IPV screening tools. Specifically, a 5-item screener has been validated to detect probable IPV in primary care settings [9, 32], but feedback from the field to Women's Health Services leadership suggests the length of the 5-item screener may represent an implementation barrier in busy practices. Thus, as a secondary aim, we will compare the utility of the 5-item screener to a 1-item screener. Consistent with the RE-AIM Framework, the proposed research has the following specific aims:
Estimate the degree of reach, adoption, implementation fidelity, and maintenance achieved using two different implementation strategies (toolkit + IAU vs. toolkit + implementation facilitation) (implementation aim)Evaluate the clinical effectiveness of IPV screening programs, as evidenced by disclosure rates and post-screening psychosocial service use (i.e., social work and mental health services uptake) (clinical effectiveness aim)2a. Compare the clinical effectiveness of two IPV screening tools (5-item vs. 1-item screener) in terms of disclosure rates and post-screening psychosocial service useIdentify multi-level barriers to and facilitators of IPV screening program implementation and sustainment

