### Quantitative evaluation of the implementation outcomes

We propose to use RE-AIM as an evaluation framework to guide our qualitative analyses [30]. RE-AIM examines 5 dimensions: reach into the target population, effectiveness of the intervention, adoption by the setting, implementation fidelity, and maintenance (i.e., degree of sustainment over time). Of these, one (effectiveness of the intervention) pertains to clinical effectiveness (aim 2), while the remaining four relate to implementation (aims 1 and 3). Thus, RE-AIM is ideal for structuring the proposed hybrid implementation-effectiveness evaluation. Table 2 describes the specific outcome measures and data sources for each RE-AIM dimension. Given our hybrid type 2 design, we are equally interested in implementation and clinical effectiveness outcomes. For this program evaluation, our primary implementation outcome will be reach (i.e., the proportion of WVs eligible for IPV screening who receive the screening). Our primary clinical effectiveness outcome will be disclosure rates and post-screening psychosocial care use (i.e., the proportion of women with a positive IPV screen who accept a referral and use psychosocial services in the ensuing 2 months).

**Table 2 Tab2:** RE-AIM guides evaluation of the impact and clinical effectiveness of IPV screening programs

RE-AIM dimension (study aim)	Outcome measures	Numerator	Denominator	Data sources
Reach (aim 1): The proportion of eligible WVs receiving IPV screening program.	Proportion of WVs seen in primary care clinics during the last 3 months of each study phase who receive IPV screening	WVs who receive IPV screening as indicated by documentation (templated note, clinical reminder)	WVs seen in primary care clinics who are eligible for IPV screening (WVs seen in clinic with no screen in prior year)	VA Corporate Data Warehouse (CDW): IPV screening status from health factors in templated notes and clinical reminders
Effectiveness (aim 2): The clinical effectiveness of IPV screening programs on disclosure and post-screening psychosocial service use.	a. Proportion of eligible WVs who screen positive for IPV	a. WVs who screen positive for IPV	a. WVs who were screened for IPV	CDW: IPV screening status, responses, and referral disposition (accept or decline referrals) from health factors in note templates and clinical reminders; psychosocial service visits based on clinic stop codes

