	b. Proportion of WVs accepting psychosocial service referrals who use such services within 2 months	b. WVs who accepted referral and who use ≥ 1 psychosocial services within 2 months after positive screen	b. WVs who screen positive for IPV and accept a referral	
Adoption (aim 1): The absolute number/proportion of primary care clinics using the IPV screening program.	a. Proportion of primary care clinics completing IPV screening with at least 70% of eligible WVs during evaluation periods	a. Primary care clinics completing IPV screening with at least 70% of eligible WVs during evaluation periods	a. All primary care clinics who saw at least one WV eligible for IPV screening during evaluation periods	CDW: WV patient encounters within primary care clinics. IPV screening status from health factors in note templates and clinical reminders. IPV screening status, resource provision, and referrals offered determined by checkboxes as health factors in note templates and clinical reminders
	b. Proportion of primary care clinics delivering IPV screening program to at least 70% of eligible WVs during evaluation periods, including evidence of resource provision and referral offered for those with positive screens	b. Primary care clinics delivering the IPV screening program to at least 70% of eligible WVs during evaluation periods, including evidence of resource provision and referral offered for those with positive screens	b. All primary care clinics who saw at least one WV eligible for IPV screening during evaluation periods	
Implementation fidelity (aim 1): The extent to which IPV screening programs are conducted as intended by clinics.	Proportion of clinics for whom at least 60% of WVs accepting referrals attend psychosocial services within 2 months of positive screen Note: Additionally assessed via key informant interviews	Primary care clinics for whom at least 60% of WVs accepting referral attend 1 + psychosocial visits within the ensuing 2 months	All primary care clinics who referred at least one screen-positive WV to psychosocial services	CDW: IPV screening status, responses, and referral disposition (accept or decline referrals) from health factors in templated notes and clinical reminders; psychosocial service visits based on clinic stop codes

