Maintenance (aims 1 and 3): The degree to which IPV screening programs are sustained over time.	Repeat Reach analysis in last 3 months of study. Note: Implementation strategies and contextual factors impacting maintenance will be assessed via survey and key informant interviews	Same as Reach analysis above, but with data collection occurring 9–12 months after IF ends	Same as Reach analysis above, but with data collection occurring 9–12 months after IF ends	CDW: For repeat of Reach analysis

We will extract relevant administrative and clinical data for all VAMCs from the VA Corporate Data Warehouse (CDW) for all five dimensions of RE-AIM (see Table 1 below for details). The templated note or clinical reminder is required for the study and includes health factors for IPV screening (i.e., disclosure), response (i.e., resources provided), and referrals offered (i.e., accepted or declined IPV Assistance Program-Coordinator referral; accepted or declined psychosocial services referral). Psychosocial care use, and time to first post-screening psychosocial care use, also come from CDW based on clinic stop codes for social work, psychology, psychiatry, primary care mental health integration, drug or alcohol treatment, and housing services.

Our operation partners are interested in testing whether a brief 1-item screener can be as effective as a more comprehensive (but lengthier) 5-item screener a modified Hurt, Insult, Threaten, Scream tool [40], which has been validated for use with the WV population [9, 32]. The tool asks individuals to indicate how often in the past year a current or past partner has done any of the following: “insulted or talked down to you,” “screamed or cursed at you,” “threatened you with harm,” “physically hurt you,” or “pressured or forced you to have sexual activities.” Response options for each item ranges from 1 (never) to 5 (frequently). Endorsement of any item indicates a positive screen. A more efficient screening tool could potentially enhance the uptake of IPV screening programs. However, prior to formal adoption of a 1-item tool, it is critical to evaluate the effectiveness of the tool in eliciting IPV disclosures (sub-aim 2a). The item was developed by a panel of IPV and women’s health clinical experts and researchers and consists of “In the past 12 months, have you experienced insulting, screaming, threatening, hitting, or unwanted sexual activity by a former or current partner?”

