We will repeat these analyses to compare the clinical effectiveness of the 5-item tool and 1-item tool as well. To evaluate the extent to which IPV screening programs facilitate timely access to psychosocial services, we compare the median number of days to first new psychosocial service visits following a positive screen for women who accepted referrals during and after the IF + toolkit implementation period. In sum, our GEE analyses will allow us to determine the extent to which changes in the quantitative outcome measures described in Table 2 prior to the implementation facilitation differ along two dimensions: (1) based on the changes during and after the implementation period and (2) based on the use of the 5-item vs. 1-item screener.

We will supplement these quantitative data, derived from the CDW, with a 50-item electronic survey to all internal facilitators at pre-facilitation, post-facilitation, and the sustainment phases to assess the use of discrete implementation strategies at each site during each study period. The survey assesses 50 of the 73 strategies described by the Expert Recommendations for Implementing Change (ERIC) study [44], which has shown validity when strategies are assessed via survey [45]. To reduce participant burden, only the 50 strategies most germane to the IPV screening program implementation are queried (i.e., excluded financial incentives as this is irrelevant in VA) and we also inquire about the perceived effectiveness of each strategy on a Likert-type scale. The responses will inform a deeper dive into the use and perceived effectiveness of implementation strategies in subsequent internal facilitator interviews (see Qualitative evaluation of the implementation outcomes and adaptations made to IPV screening programs section).

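### The 5-item vs 1-item comparison is scoped two ways, and its named outcomes count only women already screened, so differences in uptake can distort or reverse the ranking

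*Protocol article*

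**What the plan says.** **Why a short tool is considered.** The Aims section reports feedback from the field that "the length of the 5-item screener may represent an implementation barrier in busy practices". The section on quantitative evaluation of implementation outcomes adds: "A more efficient screening tool could potentially enhance the uptake of IPV screening programs".

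**What sub-aim 2a compares.** The Aims section states: "Compare the clinical effectiveness of two IPV screening tools (5-item vs. 1-item screener) in terms of disclosure rates and post-screening psychosocial service" use. Reach is not named there; it belongs to aim 1, the contrast between implementation strategies.

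**How the outcomes are built (Table 2, Effectiveness row).** The disclosure measure is headed "a. Proportion of eligible WVs who screen positive for IPV", but its denominator is "a. WVs who were screened for IPV". The denominator for service use is "b. WVs who screen positive for IPV and accept a referral".

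**What the analysis text says.** After describing the GEE models, the same section states: "We will repeat these analyses to compare the clinical effectiveness of the 5-item tool and 1-item tool as well". The closing sentence of that paragraph is broader. It says the models will show how changes in the Table 2 measures differ by screener type, and Table 2 includes Reach, Adoption and Maintenance.

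**How screeners are assigned.** Under Stepped wedge trial design, sites within each wave are assigned to one tool or the other through the balancing algorithm.

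**The concern.** There are three linked difficulties.

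1. **Scope.** The aim and the opening analysis sentence cover clinical effectiveness; the closing sentence covers every Table 2 measure. A reader cannot tell whether reach by screener is a planned result of sub-aim 2a or a by-product.
2. **Comparability.** Assignment by site supports comparisons among the eligible women at those sites. Being screened happens after assignment and may depend on the tool, since higher uptake is the reason for shortening it. If the tools lead to different women being screened, disclosure among the screened mixes the tool's ability to elicit disclosure with who was asked.
3. **Label.** Table 2 describes disclosure per eligible woman and computes it per screened woman. The two quantities answer different questions, and they can order the tools differently.

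At stake is how the screener result is read when formal adoption of the 1-item tool is considered. A lower disclosure proportion could be taken as poorer case-finding when more women were in fact identified.

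**Working it through.** **No figure of the plan's own to reproduce.** The Power analyses section claims power above 90% for reach (aim 1) and for post-screening psychosocial visits (aim 2). It gives no figure for sub-aim 2a, and the article does not print the inputs. The point does not depend on power.

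**Inputs**
- Positivity among women screened with the 5-item tool, d5 = 19%. This borrows the past-year prevalence given in the Background; using it as screen positivity is an assumption.
- Reach with the 5-item tool (r5) and the 1-item tool (r1), and positivity with the 1-item tool (d1). The article gives none of these, so all values are assumed.

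**Formulas**
- Women identified per 1,000 eligible = 1,000 × reach × positivity among the screened.
- The 1-item tool ranks lower on disclosure but identifies more women when d1 < d5 and r1 × d1 > r5 × d5. The break-even is d1 = d5 × r5 / r1.

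**Case A: dilution alone, tools equally good at eliciting disclosure.** Take r5 = 50% and r1 = 70%. Suppose 500 of every 1,000 eligible women would be screened with either tool and are 19% positive. The short tool reaches 200 more, with positivity e.
- 5-item: 500 × 0.19 = 95 identified; disclosure 19%.
- 1-item: (95 + 200e) identified; disclosure (95 + 200e) / 700.

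| e (assumed) | Identified per 1,000, 1-item | Disclosure among screened, 1-item | 5-item for comparison |
|---|---|---|---|
| 5% | 105 | 15.0% | 95; 19% |
| 10% | 115 | 16.4% | 95; 19% |
| 15% | 125 | 17.9% | 95; 19% |

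In every row the 1-item tool is lower on disclosure among the screened and higher on women identified, with no difference in how well it elicits disclosure.

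**Case B: the 1-item tool elicits less disclosure.** Break-even d1 for assumed pairs of reach, with d5 = 19%:

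| r5 | r1 | Break-even d1 |
|---|---|---|
| 40% | 50% | 15.2% |
| 40% | 60% | 12.7% |
| 50% | 60% | 15.8% |
| 50% | 70% | 13.6% |
| 60% | 70% | 16.3% |
| 60% | 80% | 14.2% |

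For example, 0.19 × 0.50 / 0.70 = 13.6%. At those reach values, d1 = 16% gives 1,000 × 0.70 × 0.16 = 112 identified against 95, although 16% is below 19%.

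**Counter-example.** With r5 = 60%, r1 = 70% and d1 = 16%, the 1-item tool identifies 1,000 × 0.70 × 0.16 = 112 and the 5-item tool 1,000 × 0.60 × 0.19 = 114. Both measures then favour the 5-item tool.

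Disclosure among the screened cannot by itself separate these situations. Shown beside reach and the per-eligible yield, it can.

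**The case against.** **Reach is already planned.** The GEE approach is said to apply to all five RE-AIM domains, and the closing analysis sentence extends the screener contrast to the Table 2 measures. This stands. A reader might infer from sub-aim 2a that uptake is wholly left out of the screener comparison; the article does not support that. What remains is that the aim and the opening analysis sentence are narrower than the closing one, and that no per-eligible yield is clearly defined.

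**Testing disclosure is deliberate.** Before formal adoption of the 1-item tool, the article says, "it is critical to evaluate the effectiveness of the tool in eliciting IPV disclosures (sub-aim 2a"). The 5-item tool is described as validated, whereas the single item came from an expert panel. Disclosure among women actually asked is the direct measure of that worry, and yield per eligible woman could favour a tool that misses more of those asked but makes it up in volume. This stands, and it is why disclosure among the screened should stay. Nor should a reader conclude that adoption must rest on a joint measure: the article states no adoption rule, and weighing yield against missed disclosures is a judgement for the partners.

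**The contrast is not one-directional.** One might infer that the comparison can only show harm or no difference for the 1-item tool. Nothing in the article implies this; the single question could produce higher disclosure.

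**Balance and covariates.** Sites are balanced across screener types, and the models include patient covariates such as age, mental health diagnoses and recent psychosocial service use. This helps in part. Site balance precedes screening, and covariates remove selection only as far as they capture it. The Limitations section itself acknowledges patient-level factors that might affect willingness to be screened.

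**Conclusion.** The point holds in a limited form. The article gives two scopes for the screener comparison. The two outcomes it names under sub-aim 2a both lie downstream of screening, and the Table 2 label for disclosure contradicts its denominator. If uptake differs by tool, disclosure among the screened may compare differently selected women and can rank lower the tool that identifies more of them.

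The size cannot be taken from the article. Under assumed reach of 50% vs 70%, 19% positivity, and 10% positivity in the extra women reached, disclosure is 19% vs 16.4% while 95 vs 115 women per 1,000 eligible are identified. If reach does not differ by tool, the ranking cannot reverse in this way. If the extra women reached were more often positive than the rest, the distortion would favour the 1-item tool instead. This is a correction to a secondary aim, worth making because it is specific and nearly free.

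**What to change.** 1. In the Aims section, name reach by assigned screener as an outcome of sub-aim 2a, and bring the opening and closing sentences on the screener analysis into line with it.
2. Add screen-positive women per eligible woman, by assigned screener, using the Reach denominator in Table 2 and the same model. Report it beside disclosure among the screened, which is kept as the measure of how well the tool elicits disclosure.
3. In Table 2, make the disclosure label match its denominator (women screened), with the per-eligible measure on its own line.
4. State that contrasts among the screened may reflect who was screened as well as the tool.

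The cost is a few wording changes, plus one further outcome and contrast from the data warehouse extract already planned. No new data collection, sites or change to assignment is needed.
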